## Abstract

Disease or acquired damage to the central nervous system frequently causes disabling spasticity and central neuropathic pain (NP), both of which are frequent in multiple sclerosis (MS) and spinal cord injury (SCI). Patients with MS and SCI often request treatment with cannabis-based medicine (CBM). However, knowledge about effects, side effects, choice of active cannabinoids (Δ9-tetrahydrocannabinol (THC), cannabidiol (CBD) alone or in combination), and doses of CBM remains limited. Using a double-blind, parallel design in a national multicenter cohort, this study examines the effect of CBM on spasticity and NP. Patients are randomized to treatment with capsules containing either THC, CBD, THC and CBD, or placebo. Primary endpoints are patient-reported pain and spasticity on a numerical rating scale. Other endpoints include quality of life and sleep, depression and anxiety, and relief of pain and spasticity. Side-effects of CBM are described. In a sub-study, the pharmacodynamics (PD) and pharmacokinetics (PK) of oral capsule CBM are examined. We expect that the study will contribute to the literature by providing information on the effects and side-effects of CBD, THC, and the combination of the two for central neuropathic pain and spasticity. Furthermore, we will describe the PD/PK of THC and CBD in a patient population.

## 1. Introduction

Disease or acquired damage to the central nervous system (CNS) may entail disabling spasticity and central neuropathic pain (NP) [1]. In patients diagnosed with multiple sclerosis (MS) or spinal cord injury (SCI), these symptoms are frequent and prominent.

MS causes multifocal and diffuse injuries to the CNS. Over time, most patients with MS (pwMS) develop significant symptoms with loss of function and a certain degree of disability. About 65% of pwMS report pain, and approximately 26% have central NP [2], which significantly impacts their quality of life [3]. About 2/3 of pwMS suffer from spasticity (tightness/stiffness of the muscles) [4] and 15% of pwMS report spasm-related pain [2]. Spasticity and spasms often have a significant impact on sleep [5] and everyday life, and are limiting factors in rehabilitation. 

The consequences of SCI depend on the neurological level and the extent of the injury. Approximately 50% of patients with SCI (pwSCI) report significant chronic central or peripheral NP [6]. In a recent Danish questionnaire survey in pwSCI, 71% reported spasticity and 46% received medical treatment for spasticity [7]. No curative treatment exists for SCI. Hence, a good rehabilitation offer including optimal symptomatic treatment to prevent long-term complications is important [8]. 

Traditionally, spasticity has been treated with baclofen or tizanidine, but the effects of these pharmaceuticals are often not sufficiently felt by many patients at the maximum dose [9], or they discontinue treatment due to side-effects. 

Treating NP is a challenge since the available analgesics often only have partial or no effect [10], and new treatment regimens, such as medical cannabis, are therefore being sought.

For centuries, cannabis has been used for various purposes [11]. Lately, interest in cannabis, cannabinoids, and cannabis-based medicines (CBM) for medical purposes has been growing [11,12]. CBM has been suggested as a treatment for a wide range of diseases and symptoms. For research purposes, the potential benefit of CBM for spasms, pain, and sleep disturbance are of certain interest [13,14]. Many pwMS and pwSCI have tried CBM to relieve their symptoms, or they demand treatment with CBM [15,16,17,18,19]. 

CBM is based on cannabinoids originating from the *Cannabis sativa* plant, which has more than 120 cannabinoids [20]. These cannabinoids can be produced as either natural (plant-derived) or synthetic compounds. The predominant effect of cannabinoids in humans is exercised via the cannabinoid receptor type 1 (CB_1_) and cannabinoid receptor type 2 (CB_2_) [20,21]. The most potent psychoactive cannabinoid is Δ9-tetrahydrocannabinol (THC) [22]. THC binds to the CB_1_ receptor and acts as a (partial) agonist. CB_1_ receptors are primarily found in the presynaptic part of the nervous system [11,23]. Cannabidiol (CBD) is another important cannabinoid. CBD allosterically blocks the CB_1_- and CB_2_ receptor (with low affinity) and therefore has antagonistic effects compared with THC (e.g., downsizes some of the (side-)effects of THC) [22,24,25,26]. CB_2_ receptors are primarily but not exclusively expressed in immune cells [21]. In animal studies, combination treatment (THC:CBD) is superior to THC and CBD alone [27], but the extent to which it also applies to humans is uncertain.

Whole-plant extracts have been suggested to have a better therapeutic effect than synthetic CBM because of entourage effects with terpenoids [25]. However, Bon-Miller et al. argued that the entourage theory has certain limitations because it is difficult to demonstrate and it is not clear, which compound drives the effect. Furthermore, they address the misconception that natural cannabinoids are superior to synthetic cannabinoids at the single molecule level [28]. When purifying cannabinoids from currently available pure chemotypes (whole-plant extract), it is noteworthy that CBD-predominant types all have the presence of THC (4–5% of the cannabinoid fraction) [11]; and at the time of trial approval, no plant-based CBD product fulfilled the authorities’ requirements for use in clinical trials. On the other hand, THC-predominant chemotype plants contain practically no CBD [11]. Hence, purified THC can be plant-based. Previously, these manufacturing issues were rarely addressed.

The effects and pharmacokinetics (PK) of CBM depend on the formulation and route of administration [29]. Inhalation of cannabinoids reaches a peak plasma concentration within 3–10 min. Oral formulation undergoes hepatic first-pass metabolism and its absorption can vary. Hence, the peak plasma concentration is lower with oral formulation than with inhalation and has a delay (~120 min). The potential benefits of oral formulation are symptomatic relief over a longer period (steadier plasma concentration over time) and the ease of use (to which the certainty of dose, preparation, and storage solutions should be added). However, the description of the pharmacodynamics (PD) and PK of the oral capsule CBM in a patient population is lacking [29]. 

In the past two decades, numerous studies have been conducted to determine the effects of CBM.

Previous studies on the effect of CBM for NP and spasticity have shown limited and conflicting evidence. Among these studies, those that investigated the effect of cannabis (smoked) or CBM on spasticity in pwMS have indicated a small positive effect [30,31,32,33,34,35,36]. In Denmark and several other countries, the oromucosal spray nabiximols (a cannabis extract product containing CBD and THC) has been approved as an add-on therapy for spasticity for pwMS if other treatments are ineffective [37]. Minor studies have been conducted investigating CBM for pwSCI which have shown some effect on spasticity, but sample sizes have been small [38,39]. 

Studies examining CBM for NP report divergent results. Only a few studies found a positive effect of CBM on neuropathic pain [40,41], but most studies investigating nabiximols report negative outcomes [10]. Several reviews and meta-reviews conducted on the topic of CBM and NP all conclude that there is no or very limited effect of CBM [13,42,43,44,45]. The most recent recommendation (2021) from ‘The International Association for the Study of Pain’ (IASP) does not endorse the use of cannabis and cannabinoids for treating pain due to lack of high-quality clinical evidence [46]. In summary, at this point it is difficult to determine unequivocally whether CBM has a place in the treatment regime for NP and spasticity in pwMS or pwSCI. 

The side-effects of CBM are important to acknowledge when discussing its potential use for symptomatic treatment. Of special concern is the risk of (long-term) psychiatric disease, risk of addiction, affected memory and driving skills (response retardation) [14,47,48]. Nonetheless, the adverse event (AE) profile of CBM is poorly understood. It is noteworthy that studies investigating isolated CBD for NP and spasticity are almost non-existent and that the exact interaction between CBD and THC is poorly understood. 

The aim of this study is to investigate the effects of CBD, THC, and the combination of the two on NP and spasticity in pwMS and pwSCI over a 6-week treatment period. A comprehensive description of side-effects is performed; and in a sub-study, the PK and PD of CBM capsules are examined. We expect that the study will shed further light on possible effects and immediate side-effects of THC, CBD, and their combination.

## 2. Materials and Methods

### 2.1. Study Design and Settings

The study is designed as a national multicenter randomized double-blind, placebo-controlled parallel study (RCT). Patients are randomized to one of four treatment arms: THC, CBD, THC and CBD, or placebo.

The study is coordinated by the steering committee with representatives from the Dept. of Neurology, Aarhus University Hospital (AUH); the Spinal Cord Injury Centre of Western Denmark (SCIWDK); the Danish Pain Research Center; the Dept. of Clinical Medicine, Aarhus University; the Danish Multiple Sclerosis Centre; the Dept. of Neurology, Copenhagen University Hospital-Rigshospitalet (DMSC); and the Dept. of Clinical Pharmacology, AUH. The Danish MS clinics and the two national SCI clinics participate in the study. The study plans to include 448 patients for the main study and 40 patients for the sub-study. All patients are randomized to one of four treatment arms (Figure 1). THC is naturally extracted from the *cannabis sativa* plant. CBD is synthetically produced. Maximum daily doses are THC = 22.5 mg and CBD = 45 mg. 

The treatment duration is 7 weeks in total, with endpoints evaluated at the end of the sixth week. Previous studies suggested an effect after 4–5 weeks of treatment [34,49] Standard Protocol Items: The Consolidated Standards of Reporting Trials (CONSORT) 2010 checklist and flow diagram will be used when presenting the results of the present study.

### 2.2. Study Subjects

PwMS Affiliated with or referred to one of the MS Clinics (at Neurological Departments) in Denmark. PwSCI Affiliated with or referred to one of the two National Clinics for Spinal Cord Injury in Denmark.

Eligible patients are informed about the study and recruited at the scheduled outpatient controls in the clinics. Additionally, the patient organizations for MS and SCI advertised the study on their webpages and member forums. In the case of interest in participation, participant information will be forwarded. 

Patients are screened for eligibility. Informed consent is obtained. For participation, the patient’s full medical history, clinical and neurological examination results, echocardiogram, and biochemistry will be obtained. Patients who, after a 7-day baseline period, meet all inclusion criteria and no exclusion criteria are randomized for treatment (Table 1).

A screening log is kept. Screening, inclusion, and randomization are performed by specialists in neurology or spinal cord injury at resident level or higher. We expect that more pwMS than pwSCI will be included.

#### 2.2.1. The Main Study

After 7 days of baseline registration, the treatment dose titration phase begins according to a standardized 3-week schedule. If tolerated, the dose is increased to the maximum (minor doses can be used in case of non-tolerable side-effects or if assessed by the patient to have sufficient effect on NP and/or spasticity). After the dose titration phase, the treatment is continued for 3 weeks at a steady dose, after which the drug is phased out over 1 week. A follow-up telephone consultation is performed 4 weeks after treatment. The patient keeps a diary during the entire medical trial. The patients record the average intensity on a numeric rating scale (NRS 0–10) for pain/spasticity and sleep, the use of paracetamol, change in medication, predefined titration plan, and how many capsules (project medication) they have taken per 24 h. Weekly during the dose titration phase, there will be telephone consultations. Other medications for spasticity and/or pain are continued at a stable dose. Concomitant therapies (including rehabilitation, physiotherapy, occupational therapy, splints and orthoses, etc.) and medication (including spasmolytics and analgesics (except opioids)) are maintained during the course of the study. Paracetamol is allowed as escape medicine. If a patient discontinues treatment before the scheduled time, the investigator will collect information on the cause, side-effects, and effect at the time of cessation. The patient is asked to continue the diary and participate in the medical check at week 6. If this is not possible or the patient wished to withdraw from the project, a follow-up telephone consultation will be agreed 2 weeks after the withdrawal. The patient is monitored for any AEs due to the project medicine. 

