### 2.9. Ethical Considerations and Safety

The study complies with the law on the processing of personal data. Trial participants receive both written and oral information before inclusion in the study and the voluntary nature of their participation will be emphasized. The patient may withdraw their informed consent for the project without justification at any time. Data from the project are stored electronically in REDCap^®^ (Aarhus University, Aarhus, Denmark), which can only be accessed by the project participants and monitors. REDCap^®^ is a secure web platform for building and managing online databases and surveys. Unexpected AEs are not expected, as the dose of THC and CBD in this study is at the same level or lower than in comparable studies [50]. In the study, patient safety is highly valued. Patients receive standardized treatment with a slow up-titration, and individual adjustment can be performed. Patients are associated with a single clinic, where they come for scheduled check-ups. All patients receive a personal contact card. All side-effects and AEs are documented. If an AEs are tolerable or unrelated to the study medication, treatment can continue with a close collaboration between the investigator/sponsor and the patient. If an AE is intolerable, patients are able to withdraw from treatment. SAE, SAR, and SUSAR are reported to the health authority within the timeframe set by Danish law, and a yearly safety report will be performed. Driving motorized vehicles is not permitted when on study medication. All women between menarche and post-menopause are defined as fertile, unless permanently sterile. Anticonception (as defined by the Danish Ministry of Health) should be used during and 3 months after treatment. Pregnancy tests will be performed for fertile women before enrollment and during the study.

Un-blinding will be performed after the last patient’s last visit (LPLV). If desired (stated at inclusion), study participants will receive a layman summary.

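### Patients who leave the project are followed for adverse events for 2 weeks and completers for 4, so off-drug events are ascertained unequally if project withdrawal differs by arm

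*Protocol article*

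**What the plan says.** Section 2.2.1 of the protocol article sets the course of treatment: "the treatment dose titration phase begins according to a standardized 3-week schedule", and then "the treatment is continued for 3 weeks at a steady dose, after which the drug is phased out over 1 week". For follow-up after that course it says: "A follow-up telephone consultation is performed 4 weeks after treatment". Table 2 marks side-effects and adverse events in every treatment week, in the phase-out week, and again at the follow-up contact in week 11.

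For patients who stop early, the same section gives a default path and a fallback. At the moment of stopping, "the investigator will collect information on the cause, side-effects, and effect at the time of cessation". The default then is: "The patient is asked to continue the diary and participate in the medical check at week 6". Only if that cannot be done, or if the patient wants to leave the project, does the fallback apply: "a follow-up telephone consultation will be agreed 2 weeks after the withdrawal".

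On which events are collected, section 2.2.1 says: "The patient is monitored for any AEs due to the project medicine". Section 2.9 says: "All side-effects and AEs are documented".

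The null hypothesis in section 2.6 covers adverse reactions as well as pain and spasticity. Section 2.7 compares nominal data between arms with a chi-square test.

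**The concern.** The last contact at which an adverse event can be reported depends on whether the patient left the project. Leaving happens after randomisation and may be related to the assigned treatment. A simple comparison of the proportions with an event makes no allowance for unequal observation time. If one arm loses more patients from the project, that arm has less off-drug observation per patient, and events that begin late or after the drug is stopped are less likely to be recorded there.

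The stake is limited to that class of event. It still deserves attention because section 1 promises a comprehensive description of side-effects and calls the adverse event profile poorly understood, and because the difference in follow-up is a stated rule for which the article gives no reason.

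**Working it through.** **1. The plan's own schedule.** Inputs from section 2.2.1: titration 3 weeks, steady dose 3 weeks, phase-out 1 week, follow-up call 4 weeks after treatment.
- End of treatment: 3 + 3 + 1 = week 7.
- Follow-up call: 7 + 4 = week 11. This reproduces the last column of Table 2.
- Off-drug window for completers: 11 − 7 = 4 weeks = 28 days.

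**2. Patients who leave the project.** Let the last dose be at the end of week t, with withdrawal from the project at the same time.
- Last contact: week t + 2. Off-drug window: 2 weeks = 14 days, whatever the value of t.
- With the completers' rule, the last contact would be at week t + 4. For a stop at week 1 it moves from week 3 to week 5; for a stop at week 5, from week 7 to week 9.
- The 2-week call is counted from withdrawal. A patient who leaves some time after the last dose is therefore covered for more than 14 days, so 14 days is the minimum for those who take the call.

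**3. Patients who stop the drug but stay in.** The gap from last dose to the week-6 check is 6 − t weeks: 5, 4, 3, 2 and 1 weeks for stops at the end of weeks 1 to 5. If the week-11 call is kept, the off-drug window is 11 − t weeks: 10, 9, 8, 7 and 6. The sentence on the 4-week call excludes nobody, but the article does not say outright that these patients still receive it.

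**4. Size overall.** Section 2.8 plans 448 patients, or 480 allowing for drop-out.
- Drop-out allowance: (480 − 448) / 480 = 32 / 480 = 6.7%.
- Share of off-drug person-weeks lost in the 4-week window, if a proportion d leave the project: d × (4 − 2) / 4 = d / 2.

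| d (all leaving the project entirely) | Off-drug person-weeks lost |
|---|---|
| 6.7% (planned allowance) | 3.3% |
| 10% (assumed) | 5% |
| 20% (assumed) | 10% |
| 30% (assumed) | 15% |

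**5. Size between arms.** The article gives no drop-out rate by arm, so this is an illustration. Suppose 20% leave in one arm and 6.7% in another. The off-drug time observed is 90.0% and 96.7% of the full window. If off-drug events are spread evenly over the 28 days and are equally frequent in those who leave and those who stay, the ratio of recorded off-drug events is shifted by 0.900 / 0.967 = 0.931, about 7% too low. With equal withdrawal in the two arms the factor is 1.

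**The case against.** The strongest reply is that the 2-week call is a fallback. The default after stopping the drug is to continue the diary and attend the week-6 check; section 4 repeats the request about the diary, and section 2.7 names it as a source of side-effect data. Someone who stops in week 1 and stays in has 5 weeks off drug by the week-6 check, more than a completer's 4. This stands, and it confines the point to those who leave the project or cannot follow the default path.

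A reader might infer that harms are under-counted where tolerability is worst. The documents do not support that. Section 2.9 says a patient with an intolerable event can withdraw from treatment, which leads to the default path and not out of the project. Harms that make a patient stop occur on drug, and they are covered by the weekly calls during titration, the diary, and the record taken at cessation.

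A reader might also infer that early stoppers have biochemistry and electrocardiogram either weeks off drug or never. Table 2 places both at week 3 and at the end of week 6, so anyone who stops at or after week 3 has an on-drug set due. What is done at an early termination visit is commonly left to the full protocol, which is not shown, so its absence here is no finding.

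Finally, the sentence on monitoring in section 2.2.1 could be read as requiring a causality judgement before an event is recorded. Section 2.9 provides for events unrelated to the study medication, and section 2.6 has an open item for other side-effects, so this is loose wording and not a restriction on collection.

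What the reply does not remove is the stated difference between 2 and 4 weeks.

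**Conclusion.** The point holds in a narrow form. For patients who leave the project, or who stop and cannot continue the diary and week-6 check, the off-drug window for adverse events is 14 days against 28 for completers. If project withdrawal differs by arm, late or off-drug events are ascertained unequally in the comparison of side-effects between arms.

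The size is modest. At the planned 6.7% drop-out about 3.3% of off-drug person-weeks are lost, and that assumes every drop-out leaves the project entirely. A bias between arms further requires unequal project withdrawal, for which the article gives no figure. Side-effects present at cessation are not affected. Patients who stop the drug but stay in are not affected either, on the reading that they keep the week-11 call.

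No conclusion follows about under-counting of the harms that cause patients to stop, or about laboratory and electrocardiogram data. This is a worthwhile, inexpensive improvement and not a flaw that threatens the trial.

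**What to change.** 1. Offer the call 4 weeks after last dose, already planned for completers, to every patient, including those who stop treatment or leave the project. Keep the 2-week call as an additional contact. State explicitly that patients who stop the drug but stay in also receive the 4-week call.
2. Compare adverse events between arms in one common window measured from last dose. For patients already past the point where the later call could be offered, use last dose + 14 days, which the 2-week call covers; describe later events separately. This needs only the date of last dose and the date of onset.
3. Align the sentence on adverse event monitoring in section 2.2.1 with section 2.9, so that both say that all adverse events are recorded.

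The cost is one extra telephone call for roughly 30 patients (32 at the planned allowance), plus the wording. Patients who have withdrawn may decline the call, as they may already decline the 2-week one, so some imbalance can remain; the common window deals with it in the analysis. Limiting that window to 14 days leaves completers' events from days 15 to 28 out of the between-arm comparison.

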#### 2.2.2. The Sub-Study

PK and PD are investigated in a subset of 40 patients from the main study, all recruited from AUH. The patients will be admitted to the hospital for a 24 h period while in a steady state with the project medicine (preferably week 6). During the 24 h period, pain (NRS 0–10) and side-effects are registered and blood samples collected for PK/PD (blood samples are taken before the first dose on the startup day and then at 1 h, 2 h, 4 h, 6 h, 8 h, 10 h, 12 h, 15 h, 18 h, 21 h, and 24 h after the first dose). The blood samples will be kept at −80 degrees until analysis. Blood tests are analyzed at the Institute of Legal Medicine, Dept. of Forensic Medicine, Aarhus University, where full blood will be analyzed for THC, cannabinol (CBN), and CBD; and the metabolites 11-hydroxy-Δ9-tetrahydrocannabinol (THC-OH), and 11-nor-9-carboxy-Δ9-tetrahydrocannabinol (THC-COOH) by high-throughput liquid chromatography-mass spectrometry, LC-MS-MS [51].

